### Interventions

2.9

#### Control group

2.9.1

The subjects in the control group will maintain their original lifestyle and perform routine activities of daily living. During the intervention period of 12 weeks, if the participants change their daily activities or increase their amount of exercise or exercise intensity, they will be required to record the details of the extra physical activity, including the type, intensity, and activity time.

#### Core strength training group

2.9.2

In addition to the routine activities of daily living, the participants in the CST group will receive 12 weeks of CST. The CST programme will be supervised and guided by 2 experienced physiotherapists who work in the Ningxia Hui Autonomous Region People's Hospital and will ensure that each participant is familiar with a standard CST programme. The core strength training programme consists of 5 core movements:(i)Double leg bypass: in the supine position, the participants are required to flex the hip joint, flex the knee joint, and then use their back to raise their waist and buttocks and to maintain hip extension to increase the proprioception of the back;(ii)Single leg bypass: in the supine position, the participants are required to flex the knee and hip of the left leg, keep the right leg straight, and then raise their lower back, hip, and right leg while maintaining bilateral hip extension in the air, using the shoulders and left leg only as a fulcrum, alternating twice on each side;(iii)Supine step: in the supine position, the participants are required to take a bilateral leg knee flexion, alternating the left and right feet step by step, to increase hip balance;(iv)Four-point support (abdominal bridge): in the prone position, the participants are required to use both elbows and feet as a fulcrum, with the body propped up and suspended in the air, facing front throughout the action;(v)Kneeling diagonal support: the participants will take a kneeling position, supporting the body with both hands and knees, with the arms straight, both hips flexed and a knee flexion of 90 degrees; then the left side of the upper arm will point straight forward and the right leg will point backward, so that the body will be supported only with the right hand and left knee, alternating bilaterally.

CST training will take 60 minutes per day, starting with a brief warm-up programme to prepare the body, and ending with a cool-down programme. The entire intervention length is 5 days/week, totally 12 weeks.

#### Tai Chi Chuan group

2.9.3

In addition to the routine activities of daily living, the participants in the TCC group will receive 12 weeks of TCC training. The TCC programme is composed of 24 movements from the Yang styles (http://www.egreenway.com/taichichuan/short.htm#List), which particularly involve deep breathing accompanied by the opening and closing of the hands and stepping forward and backward with weight transference.^[21]^ Before starting the TCC program, the participants will be instructed by certified TCC instructors, who will ensure that each participant is familiar with a standard TCC programme. TCC training will take 60 minutes per day; warm-up exercises of each session will be applied to the preparation of the neuromuscular system for the training loads, and sessions will end with a cool-down exercise to release muscle tension and stiffness (for example, arm swinging, simple stretching exercise, deep breathing, etc.).

The participants in the TCC training group will exercise for 5 days/week at the Ningxia Yuehai Service Center, for a total of 12 weeks.

#### Combined training group

2.9.4

In addition to the routine activities of daily living, the participants in the CTG will receive 30 minutes CST and 30 minutes TCC training per day, 5 days/week, totally 12 weeks.

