Strength training has recently become a hot topic in many clinical studies, including the elderly.^[12,13]^ There are many studies indicating that strength training can improve the mobility of the human body (e.g., increase gait speed and distance), functional tasks (e.g., standing and shifting), and basic daily life functions of the elderly.^[14,15]^ In many sports activities, people have been increasingly aware of the importance of the central core of the body for stabilization and power generation. “Core stability’” refers to the ability to control the position and movement of the trunk over the pelvis so as to make the best production, transfer, and control of force and motion to the terminal segment during the comprehensive movement. Rehabilitation should include the restoration of the core itself and the core as the base for extremity function.^[16,17]^ In a recent study, the researchers conducted a nine-week progressive core strength training (CST) study on the unstable surface among the elderly in the community. It was concluded that CST conducted on unstable surfaces is a feasible and effective exercise programme to alleviate age-related performance decline.^[18]^

As mentioned above, both methods of physical training have positive effects on the outcome of human health. However, it is difficult to draw firm conclusions because limitations or biases exist in most studies due to factors such as insufficient sample size or a lack of strict randomized design. In addition, there is no systematic comparison of the effects of TCC and CST, nor has the possibility of a synergistic effect of the two physical training combinations been evaluated. The aims of this study protocol are to evaluate the effects of CST compared to those of TCC on the outcomes of the musculoskeletal system and cardiopulmonary function in older adults and to test the synergistic effect of a combined physical training of CST and TCC.

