### Study design and setting

2.1

This study is a randomized, single-blind, parallel-controlled trial. Participants will be randomly allocated into 4 groups:(i)control group (CG): routine activities of daily living;(ii)CST group: routine activities of daily living plus core strength training;(iii)TCC group: routine activities of daily living plus TCC; and(iv)combined training group (CTG): routine activities of daily living plus core strength training and Tai Chi Chuan.

All participants will receive the same intervention time of 1 hour/day, 5 days/week for a total of 12 weeks. Both musculoskeletal and cardiopulmonary function outcomes, including bone density detection, balance and co-ordination ability, walking ability, pain visual analogue scale (VAS) score, fall risk assessment, activities of daily living, pulmonary function test, color sonography, and electrocardiogram will be evaluated by the blinded assessors at the People's Hospital of Ningxia Hui Autonomous Region at baseline, at 13 weeks (end of the intervention), and at 25 weeks (12 weeks after follow up). At the end of each month during the intervention period, there will be professional trainers to guide the participants to ensure that the participants are trained correctly. The flow diagram of the entire trial programme is illustrated in Figure 1.

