### Sample size

2.2

We used change in bone mineral density (BMD) as the main effect indicator to estimate the sample size. Sample size calculations are performed to determine the number of participants necessary to detect effect sizes. Very few randomized controlled trials have examined the effect of TCC or CST on BMD in the elderly.

Based on similar previous studies^[19,20]^ and our preliminary experiment, the means with SDs of the BMD (lumbar spine) were X1 = 0.007 (SD1 = 0.098), X2 = 0.043 (SD2 = 0.108), X3 = 0.021 (SD3 = 0.0915), and X4 = 0.051 (SD4 = 0.099) in the CG, CST, TCC, and CTG, respectively. The sample sizes per group were calculated according to the formula: 

(i)with a type I error of 5% (α = 0.05) and 80% power (β = 0.10).(ii)K: groups, K = 4.(iii)Ψ: K = 4, V1 = K-1 = 3; V2 = N-1, N desirable maximum, Ψα, β, K-1,∞ = 2.17 (Obtained from statistical tables).(iv)X0 = (X1 + X2 + X3 + X4)/K = 0.0305.

We can calculate the number of samples as n≈80, considering a 20% dropout and exit rate. Thus, a minimum of 384 total participants is necessary to reach the target of 96 participants per group.

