### Limitations

3.1

As with most clinical studies, there are also obvious limitations in this study. Ideally, all participants in clinical randomized controlled trials should follow the blind method, but this is difficult to achieve in non-pharmacological trials.^[42]^ Although it is impossible to conduct blinding of both the coaches and participants in this trial, we will reduce the possible bias by blinding the assessors and data analysts.

In summary, the results of this trial are expected to clarify the synergistic effect of CST and TCC training on musculoskeletal and cardiopulmonary function in older adults and to confirm whether combined or exclusive CST and TCC training, is more effective at improving functional outcomes in the elderly.

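### The combined arm halves each training to hold total time at one hour, so the trial cannot show the synergistic effect it promises; it can only compare combined with single training at equal time

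*Protocol article*

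**What the plan says.** Section 2.1 fixes a common training time: "All participants will receive the same intervention time of 1 hour/day, 5 days/week for a total of 12 weeks". Sections 2.9.2 to 2.9.4 divide it among the three training arms:

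- CST arm: "CST training will take 60 minutes per day, starting with a brief warm-up programme to prepare the body".
- TCC arm: "TCC training will take 60 minutes per day".
- Combined arm (CTG): "the participants in the CTG will receive 30 minutes CST and 30 minutes TCC training per day".

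The control group (CG) keeps its usual activities.

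The article words its purpose in two ways. The last paragraph of the Introduction gives as an aim "to test the synergistic effect of a combined physical training of CST and TCC", and section 3.1 closes by saying that "the results of this trial are expected to clarify the synergistic effect of CST and TCC training on musculoskeletal and cardiopulmonary function in older adults". The Discussion part of the Abstract makes the same promise, and section 3 names the lack of evidence on synergy as one of the two issues the trial should settle. By contrast, the Background of the Abstract words the second objective simply as testing whether combined training is effective. The Abstract and section 3.1 also ask whether combined training or one training by itself works better. Synergy is not defined.

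Section 2.2 gives planning means (SD) for lumbar spine bone mineral density, "in the CG, CST, TCC, and CTG, respectively": 0.007 (0.098), 0.043 (0.108), 0.021 (0.0915) and 0.051 (0.099).

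**The concern.** Synergy means that two trainings together do more than the sum of what each would do separately, in the amounts in which they are combined. To see it, one must know what each component achieves at the amount used in the combination. Here the combination uses 30 minutes of each, while each component is observed alone only at 60 minutes. Any gap between the combined arm and the single arms therefore mixes two things: how the trainings act together, and how much benefit is lost when each is cut to half its time.

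An analysis plan can name a contrast, but it cannot supply the missing information, because that depends on the arms fixed here. What is at stake is the conclusion: the article tells readers to expect an answer about synergy that the data cannot give under any analysis without an outside assumption.

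**Working it through.** **Inputs.** Nominal daily minutes come from sections 2.9.2 to 2.9.4, and means and SDs from section 2.2. As a check on reading the means, (0.007 + 0.043 + 0.021 + 0.051)/4 = 0.122/4 = 0.0305, which matches the grand mean in section 2.2. The plan gives no figure for synergy. Its group sizes (80, or 96 with the dropout allowance) are used only as group sizes; how they were derived is a separate matter.

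**Step 1: which amounts are observed (minutes per day).**

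| Arm | CST | TCC |
|---|---|---|
| CG | 0 | 0 |
| CST | 60 | 0 |
| TCC | 0 | 60 |
| CTG | 30 | 30 |

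The cells (30, 0) and (0, 30), needed for synergy at the combined amounts, are absent. So is (60, 60), needed for synergy at the full amounts.

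**Step 2: effects over control on the planning means.**

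- CST: 0.043 − 0.007 = 0.036
- TCC: 0.021 − 0.007 = 0.014
- CTG: 0.051 − 0.007 = 0.044

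**Step 3: two additive benchmarks.**

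- If 30 minutes keeps the full effect: 0.036 + 0.014 = 0.050. CTG minus this is 0.044 − 0.050 = −0.006, the same as CTG − CST − TCC + CG.
- If 30 minutes keeps half the effect: 0.018 + 0.007 = 0.025. CTG minus this is 0.044 − 0.025 = +0.019, the same as CTG − (CST + TCC)/2 = 0.051 − 0.032.

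**Step 4: between the benchmarks.** Let 30 minutes keep a fraction f of the 60-minute effect, the same f for both trainings (an assumption made for simplicity). Then synergy = 0.044 − 0.050f.

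| f | Apparent synergy |
|---|---|
| 0.5 | +0.019 |
| 0.7 | +0.009 |
| 0.8 | +0.004 |
| 0.88 | 0 |
| 1.0 | −0.006 |

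The sign changes at f = 0.044/0.050 = 0.88. By step 1, no arm allows f to be estimated.

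**Step 5: precision of the contrasts.** SE = √(Σc²SD²/n), with c the contrast weights. Power is two-sided at 0.05, by normal approximation, with no multiplicity adjustment.

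| Contrast | Value | SE, n = 96 | Power, n = 80 | Power, n = 96 |
|---|---|---|---|---|
| CTG − CST | +0.008 | 0.0150 | 8% | 8% |
| CTG − TCC | +0.030 | 0.0138 | 51% | 59% |
| CTG − (CST + TCC)/2 | +0.019 | 0.0124 | 29% | 33% |
| CTG − CST − TCC + CG | −0.006 | 0.0203 | 6% | 6% |

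For example, the SE of CTG − CST is √((0.099² + 0.108²)/96) = 0.0150, giving a 95% half-width of 1.96 × 0.0150 = 0.029 around an expected difference of 0.008.

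**The case against.** The best defence is that equal total time is a deliberate and sensible choice: it keeps extra training volume from explaining a better result in the combined arm. The article describes a parallel-group trial, never a factorial one, and never mentions an interaction. The second objective as worded in the Abstract, and the question of combined against single training, are both within reach. All of this stands, and it is why the arms need no change. It does not rescue the synergy wording, which the Introduction and the closing summary state outright.

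Four stronger readings are tempting, and the documents do not support them.

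- *The trial is a failed factorial that can estimate no joint effect.* The article never claims a factorial design. The equal-time contrast CTG − (CST + TCC)/2 can be estimated; only its reading as synergy needs an assumption.
- *The planning means already point to synergy, or against it.* They come from earlier studies and a pilot whose training times are not given, and the two contrasts answer different questions. Both are also small against their standard errors (0.019 against 0.0124, and 0.006 against 0.0203, at 96 per arm).
- *No synergy analysis is planned, so the definition will be picked after the data.* Contrasts are commonly left to a statistical analysis plan, which is not shown. Their absence from an article proves nothing.
- *A combined-versus-control difference will be reported as synergy.* Nothing in the article says so.

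**Conclusion.** The point holds as a mismatch between a stated aim and the arms. With 60 minutes of one training set against 30 + 30 minutes of both, synergy is confounded with the unknown effect of halving each training, and no analysis plan can undo that. The comparison of arms at equal total time is sound.

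The confounding itself follows from the training times alone. The size is illustrative: on the planning means the answer runs from −0.006 to +0.019 as the fraction of benefit kept at half time goes from 1 to 0.5, crossing zero at 0.88. That range assumes that the means reflect the planned training times, which the article does not state, and that one common fraction applies to both trainings.

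**What to change.** Keep the arms as they are. In the Abstract, the last paragraph of the Introduction, section 3 and section 3.1, replace the synergy wording in the aims and expected conclusions with: *combined training compared with CST alone and TCC alone at equal total training time*. This also brings these places into line with the second objective in the Abstract.

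Report CTG − CST and CTG − TCC as estimates with confidence intervals. CTG − (CST + TCC)/2 may be added, with a statement that it can be read as synergy only if benefit is proportional to training time, which the trial cannot check.

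The cost is a few sentences and a narrower claim. Precision will be low: on the planning means CTG − CST has about 8% power at 80 or 96 per arm. For that reason I would not make a conclusion depend on the combined arm beating both single arms, since such a rule could succeed at most about 8% of the time on those means.

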### Follow-up period

2.10

During the 12 weeks follow-up period, all participants will be told to resume their original lifestyle without having to insist on special exercise intervention. In addition, if the participants cannot avoid an increase in exercise load, they will be required to record the details of the extra physical activity, including the type, intensity, and time. We will re-measure the primary outcomes at the end of the follow-up period.

### Outcome assessment

2.11

The outcome assessment is mainly composed of three parts:(i)musculoskeletal system index: bone mineral density, balance ability, flexibility, fall risk assessment, and so on;(ii)cardiopulmonary function evaluation index: a step test, vital capacity, heart rate, and so on; and(iii)other related indexes: activities of daily living, pain score, QOL, and so on.

All primary and secondary outcomes will be assessed by experienced therapists at the rehabilitation department of the People's Hospital of Ningxia Hui Autonomous Region at baseline and at 12 weeks (the end of the intervention). The process of the assessments is listed in Table 1.

### Primary outcomes

2.12

#### Bone mineral density (BMD)

2.12.1

We will assign a professional technician to perform standard BMD measurements by using DXA (GE Lunar iDXA with encore 12.0 software, GE Healthcare Lunar, Madison, WI).^[22]^ BMD measurements includes the whole body, lumbar spine (L1-L4), proximal femur of the left leg, and left fore-arm.^[23]^ In order to ensure the accuracy of the collected data, all instruments should be calibrated by the inspector before the measurement is carried out.

#### Cardiopulmonary function

2.12.2

Cardiopulmonary function in this study will be evaluated by step test, vital capacity, blood pressure and heart rate. The step test will be carried out using a step tester (product type: CSTF-TZ-5000) manufactured by Beijing Titanium Oriental Co., Ltd. The vital capacity was measured using a vital capacity tester (product type: CSTF-FH-5000) produced by Beijing Zhongtai Oriental Co., Ltd. Blood pressure and resting heart rate will be tested by an electric sphygmomanometer produced by Omron, Dalian, China (product type: HEM-76C).

#### Secondary outcomes

2.12.3

The balance ability will be measured by standing on the Pro-kin system (product type: PK254P; produced by Tecnobody S.r.l company, Italy) with eyes open for 30 seconds and eyes closed for 30 seconds. The Flexibility will be measured using Sit and Reach flexibility test equipment (product type: CSTF-TQ-5000, Zhongtitongfang Co., Ltd., Beijing, China). Fall risk will be assessed via the short-form Falls Efficacy Scale International.^[24]^ Activities of daily living will be assessed using the Chinese version of the Instrumental Activities of Daily Living (IADL).^[25]^We chose the VAS as the pain score, which is1 of the most commonly used pain intensity measurement (0∼4 mm can be regarded as no pain; 5∼44 mm represents mild pain; 45∼74 mm represents moderate pain; 75∼100 mm represents severe pain).^[26]^ QOL will be evaluated using the Chinese version of EQ-5D-5L.^[27]^

#### Safety evaluation

2.12.4

Although there are few reports on the adverse events (AEs) of TCC exercise, any unexpected AEs during the intervention period such as lumbar sprain, knee or ankle sprain, and knee pain, etc. will be recorded in detail on a case report form (CRF). If serious AEs occur, the researchers will report immediately to the project leader and the ethics committee, and they will decide whether the participants need to withdraw from the research after negotiation.

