### Withdrawal criteria

2.6

Participants who meet1 of the following conditions will be withdrawn from the trial:(i)failure to train as required after the experiment;(ii)suffer from bone or joint pain that impacts the continuation of training;(iii)unable to continue training due to other diseases;(iv)assigned to the control group but followed a regular exercise programme.

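### The adverse-event rule's word *unexpected* conflicts with its own examples, and recording of non-serious events is stated only for the 12-week intervention although follow-up runs to week 25

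*Protocol article*

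**What the plan says.** Section 2.12.4 (Safety evaluation) gives one rule for entering adverse events in general on the case report form: "any unexpected AEs during the intervention period such as lumbar sprain, knee or ankle sprain, and knee pain, etc. will be recorded in detail". A separate sentence covers serious events: "If serious AEs occur, the researchers will report immediately to the project leader and the ethics committee". That sentence has no time limit and no test of expectedness.

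Section 2.6 (Withdrawal criteria) lists, among the reasons for leaving the trial, that participants "suffer from bone or joint pain that impacts the continuation of training". Section 2.9.1 gives the intervention as 12 weeks. Section 2.10 then describes what happens afterwards: "During the 12 weeks follow-up period, all participants will be told to resume their original lifestyle". Sections 2.1 and 2.12.5 place a further assessment at week 25. Section 2.8 states that participants and training instructors cannot be blinded.

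**The concern.** A rule for recording harms should let two people faced with the same event make the same decision, whichever arm the participant is in. This one attaches a qualifier that its own examples do not meet. A lumbar sprain or a sore knee is what one would foresee in older people starting an hour of daily training, and section 2.6 already foresees joint pain that interrupts it. Staff who go by the qualifier and staff who go by the examples could record different things.

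The rule also names a period, the intervention, that is shorter than the period for which participants stay under observation. A musculoskeletal complaint that persists or first appears after training stops has no stated place in the non-serious safety data.

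At stake are the completeness of the harms counts and their comparability across four arms, in a trial meant to say whether combined or single training serves older adults better.

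**Working it through.** The plan gives no event rate or safety figure, so there is nothing to reproduce. The check sets the sections side by side, with one simple ratio.

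**1. Qualifier against examples (2.12.4, 2.6, 2.9.2).**
- The named injuries (lumbar, knee or ankle sprain, and knee pain) are to be recorded under any sensible reading, because the sentence lists them.
- The ambiguity bites on foreseeable complaints that are not listed. An illustration is wrist or shoulder pain after the hand-and-knee support exercise in 2.9.2. If *unexpected* governs, it can be left out. If the examples and the open-ended end of the list govern, it goes in. The text does not say which prevails.

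**2. Could the decision differ by arm (2.8)?**
- Participants and instructors know the allocation. The article does not say who applies the recording rule.
- Joint soreness is easily thought expected in someone training five days a week and unexpected in a control participant. A test of expectedness therefore gives knowledge of the arm a route into the count. This is a possible mechanism; nothing in the document shows that it will operate.

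**3. Recording window against observation period (2.12.4, 2.9.1, 2.10, 2.1).**
- Inputs: intervention 12 weeks (2.9.1); follow-up 12 weeks (2.10); last assessment at week 25 (2.1, 2.12.5).
- Share of planned time with no stated recording of non-serious events = follow-up / (intervention + follow-up) = 12 / (12 + 12) = 0.50.
- On the 25-week calendar the share is 12/25 = 0.48 if only the 12 follow-up weeks are counted, and (25 − 12)/25 = 13/25 = 0.52 if everything after week 12 is counted. The answer is about half on any of these counts.

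**4. Serious events (2.12.4).** The reporting sentence carries neither the window nor the qualifier. The gap in step 3 concerns non-serious events only.

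**5. Withdrawal for pain (2.6, 2.14).** Pain that stops training arises during the intervention, so it falls inside the recording window. Section 2.14 adds an attempt at a last evaluation before the participant leaves. These sections do not show that such events are lost.

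**The case against.** The strongest reply has four parts.

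- **The wording is loose, but the meaning is clear.** Given the examples, *unexpected* probably means untoward. A reader might infer that foreseeable training injuries are excluded from the safety data. The documents do not support that, because the sentence names exactly such injuries as recordable. What remains is that the text, followed literally, permits a different decision for unlisted events.
- **The window follows exposure.** In follow-up nobody is asked to keep training, so restricting routine recording to the training period in a low-risk exercise trial can be defended. A reader might infer that every event after week 12 goes unrecorded. That is also too strong, since serious events are reported without a time limit. The reply does not remove the gap for non-serious complaints that persist or appear later, in people who are seen again at week 25 anyway.
- **The article is condensed.** It says what will be recorded, not that nothing else will be, and a full protocol may hold further procedures. This is fair, and it is why missing definitions or forms are not part of the point. The two limits, however, are stated in the article's own text.
- **No bias is shown.** A reader might infer that the safety comparison is biased. The documents show only a risk. The mechanism bears mainly on exercise against control, not on the three training arms against each other, and no formal safety comparison is planned. Nor does it count against the rule that falls are not named, because the list of examples is left open.

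The reply reduces the point to one of wording and window. It does not dispose of it.

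**Conclusion.** The point holds in a narrow form. The qualifier conflicts with the rule's own examples and leaves room for uneven recording, possibly by arm. Non-serious events have a stated recording period covering about half of planned observation (12 of 24 weeks; 48% to 52% without recording on the 25-week calendar). Serious-event reporting is unaffected.

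This rests on two assumptions: that the published sentence is the operative rule, and that no fuller document widens it. The number of events that might be missed, and the size or direction of any difference between arms, cannot be computed from the document. No efficacy conclusion depends on it. It is a cheap improvement, not a flaw that threatens the trial.

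**What to change.** In section 2.12.4, replace "any unexpected AEs during the intervention period" with: *all adverse events, whether or not expected, in all four groups from randomisation to the week-25 assessment*. Keep the examples and the serious-event sentence as they are.

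Add that the same question is asked in every arm at the existing contacts, and that events are reported by randomised group. The contacts are the end-of-intervention assessment (or the last evaluation before withdrawal) and the week-25 assessment. Section 2.1 puts the end-of-intervention assessment at week 13, while 2.11 and 2.12.5 put it at week 12, so the sentence should use whichever label is settled on.

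One practical point: an account of an injury may reveal the arm, and section 2.8 asks participants not to mention their training to assessors. The question is best put by someone other than the blinded assessor, or after the outcome measurements are finished.

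The cost is a little more data collection and entry, without additional visits. Training, eligibility and withdrawal rules are untouched.
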